#### Stage 2a

Assuming a statistical significance level of 5% and a statistical power of 80%, in order to detect a 35 m difference in ISWT measured at baseline and after completion of PR,^23^ a total of 114 participants are required (PR: 57 participants or waiting list control: 57 participants). This power calculation was performed using a paired t test and assumes the ISWT follows an approximately normal distribution. Data from a feasibility study in Uganda, assessing PR in a PTBLD population, have guided this calculation.^14^ Conservatively assuming up to 30% loss to follow-up at 6 weeks, this will require up to 114 participants to be recruited and randomised (1:1) to each arm. The estimated 70% ineligibility rate suggests approximately 543 patients with PTBLD will be screened for this trial.

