### Outcomes

A schedule of events is provided in table 1 and measures are in accordance with the recommended minimum data set for PR in LMIC.^16^ In the case of a face-to-face follow-up, appointment at 12-week postbaseline cannot be conducted, questionnaires will be collected over telephone.

**Table 1 T1:** Schedule of events

	Baseline	6 weeks	12 weeks	
	Face-to-face	Face-to-face	Face-to-face	Telephone*
Sociodemographics	x			
Age of leaving full time education	x			
Smoking and biomass exposure	x			
Respiratory diagnoses	x			
Spirometry	x			
Hospitalisations in the last 12 months	x			
Comorbidities	x			
Treatments	x			
Physical activity monitoring	x	x		
Anthropometrics	x	x	x	
ISWT and ESWT	x	x	x	
5x sit to stand	x	x	x	
MRC score	x	x	x	x
EQ5D score	x	x	x	x
Pain scores for chest pain	x	x	x	x
CCQ	x	x	x	x
CAT	x	x	x	x
HADS	x	x	x	x
WPAI questionnaire	x	x	x	x

CAT, COPD Assessment Test; CCQ, Clinical COPD Questionnaire score; ESWT, Endurance Shuttle Walk Test; HADS, Hospital Anxiety and Depression Scale; ISWT, Incremental Shuttle Walk Test; MRC, Medical Research Council; WPAI, Work Productivity and Activity Impairment Questionnaire.

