### Data analysis

For stages 1 and 2b, qualitative data will be transcribed verbatim in Russian and translated into English for triangulation with UK-based researchers. Transcripts will be analysed using thematic analysis; following the six distinct stages of familiarisation with data; generating initial codes; searching for themes; reviewing themes; defining and naming themes and producing the report.^34 35^ The qualitative lead will carry out initial coding and a sample of the transcripts will be coded independently by a second researcher to improve consistency and interpretive authenticity. The team will meet regularly to review emerging themes, with close attention to interactions within the interview and focus group data.

For stage 2a, quantitative analysis will be conducted using Statistical Package for the Social Sciences. Data will be reported as mean (SD), median (IQR) or frequency (%) as appropriate. All randomised patients will be included in an intention to treat analysis with the primary efficacy analysis based on both per protocol and modified intention-to-treat populations, with missing data imputed. For the primary analysis, the differences in the primary outcome of walking distance on the ISWT will be estimated using mixed models (unadjusted and adjusted for covariates if there are differences between groups at baseline). There will be no formal interim analysis of the data.

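### Adjustment of the primary ISWT analysis depends on observed baseline differences, with no commitment to using baseline ISWT and no single primary estimate

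*Protocol article*

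**What the plan says.** In the Data analysis section, the stage 2a paragraph states that "the differences in the primary outcome of walking distance on the ISWT will be estimated using mixed models", and adds in parentheses "unadjusted and adjusted for covariates if there are differences between groups at baseline". It names no covariate, gives no test or threshold for a difference, and does not say how baseline ISWT enters the model or which of the two estimates leads.

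The schedule of events (Table 1, under Outcomes) shows the walk tests at baseline, 6 weeks and 12 weeks: "ISWT and ESWT x x x". The Randomisation section gives 1:1 allocation and names no stratification factors.

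The Sample size section for stage 2a sets alpha at 5% and power at 80%. The target is worded "in order to detect a 35 m difference in ISWT measured at baseline and after completion of PR". From this the section arrives at 57 per arm, or 114 in all. It gives neither an SD nor a correlation between baseline and follow-up ISWT.

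**The concern.** Under randomisation, a baseline difference between arms is a chance event. It is a poor reason to adjust; the sound reason is that a covariate predicts the outcome, which can be judged before any data are seen. A rule that adjusts only after a difference is found lets the observed data choose the primary model. With no covariate list and no threshold, it also leaves that choice to judgement once the baseline table by arm is known.

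Two things are at stake. The first is clarity: when the condition is met there are two estimates of the primary effect, with no stated order between them. The second is precision: baseline ISWT is likely to be a strong predictor of follow-up ISWT, and in most trials the arms will show no marked imbalance, so the rule would usually leave the adjustment out.

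**Working it through.** **Inputs from the protocol (Sample size, stage 2a).** Difference 35 m; alpha 5% (taken as two-sided, since sidedness is not stated); power 80%; 57 per arm.

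**Inputs assumed.** Correlation r between baseline and 6-week ISWT of 0.5 to 0.8; equal SDs at both visits; normal data; 57 completers per arm; a difference counted as present when a baseline t test on ISWT gives p < 0.05; baseline ISWT as the covariate.

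**The plan's own figure.** The 57 per arm cannot be reproduced, because no SD is stated. Solving backwards for a two-arm comparison of follow-up values:

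SD = 35 × √(57/2) / (1.960 + 0.842) = 66.7 m.

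This SD is used below only to anchor power at 80% for an unadjusted comparison of follow-up values. It is not a claim about the true SD.

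**Variance of the arm contrast, relative to follow-up values alone.**
- Follow-up values only: 1
- Change from baseline, or a group-by-time model with baseline as an unconstrained outcome: 2(1 − r)
- Adjusted for baseline ISWT: 1 − r²
- Adjusted relative to change: (1 − r²) / [2(1 − r)] = (1 + r)/2

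| r | Change | Adjusted | Adjusted / change |
|---|---|---|---|
| 0.5 | 1.00 | 0.75 | 0.75 |
| 0.7 | 0.60 | 0.51 | 0.85 |
| 0.8 | 0.40 | 0.36 | 0.90 |

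The reduction from follow-up values to the adjusted analysis is r²: 25%, 49% and 64%. It passes one half only when r exceeds √0.5 = 0.707.

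**Power of the conditional rule** (simulation, 40,000 trials per setting, true effect 35 m; a repeat with 100,000 trials agreed to within 0.004).

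| r | Rule, follow-up values | Rule, change | Always adjusted |
|---|---|---|---|
| 0.5 | 0.80 | 0.81 | 0.89 |
| 0.7 | 0.81 | 0.95 | 0.97 |
| 0.8 | 0.82 | 0.99 | 0.996 |

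So if the unadjusted model uses follow-up values only, the rule recovers almost none of the available gain. If it already carries baseline as an outcome, always adjusting adds about 8 to 9 points at r = 0.5, 2 at r = 0.7 and under 1 at r = 0.8. Part of that shrinkage is a ceiling effect. If 80% power were anchored on change instead, the gain would run from Φ(2.80/√0.90 − 1.96) = 0.84 to Φ(2.80/√0.75 − 1.96) = 0.90, that is, 4 to 10 points.

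**Type I error** (same simulation, no true effect; r = 0.5, 0.7, 0.8).
- Rule on follow-up values: 0.044, 0.036, 0.030
- Rule on change: 0.043, 0.044, 0.049
- Adjusted fit run only after an imbalance, and the better of the two then claimed: about 0.05 in every setting
- Both fits always run and the better claimed: 0.075, 0.084, 0.086 on follow-up values; 0.072, 0.067, 0.066 on change

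**The case against.** The strongest reply is that the protocol never says baseline ISWT is left out. The Abstract describes the test before and after PR. The sample size target is worded as a difference from baseline, and "This power calculation was performed using a paired t test and assumes the ISWT follows an approximately normal distribution". Three visits feed a mixed model. Baseline ISWT may well be a repeated outcome in that model whether or not the arms differ, with the parenthesis covering only other covariates. This stands. A reader might infer that baseline ISWT is dropped unless imbalanced and that most of its precision is thrown away; the text supports neither. Even on follow-up values alone, the variance reduction is below one half at r = 0.5, and just below at r = 0.7.

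A reader might also infer that the rule inflates the false-positive rate to 8 or 9%. That requires both fits always to be run and the better one claimed, which the plan does not describe. Under the rule as written, with the assumed trigger, the error is at or below 5%.

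A last reply is that covariate lists and the choice of leading estimate belong in the SAP, which is not shown. This is fair for the list and for the full model specification. It does not cover the condition itself, which the protocol states outright: an SAP that followed it would inherit the fault, and one that did not would depart from the published protocol.

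**Conclusion.** The point holds as a fault in a stated rule. Making adjustment depend on chance imbalance leaves the primary model to the data, without a commitment to baseline ISWT or a single leading estimate. This does not depend on any assumed number.

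The size of the loss does. It could be large (about 80 to 82% power against 89% to over 99%) if the unadjusted model uses follow-up values only, or small (about 0 to 9 points, with a remaining variance ratio of 0.75 to 0.90) if baseline is already a repeated outcome. Both ranges rest on assumed correlations of 0.5 to 0.8, a back-solved SD, 57 completers per arm and an assumed p < 0.05 trigger; the document cannot settle which applies. There is no evidence of an inflated type I error: on follow-up values the rule is conservative, at about 3 to 4%. The change is worth making because it improves clarity for certain and precision very probably.

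**What to change.** In the Data analysis section, delete the clause that makes adjustment depend on baseline differences. State instead that:

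- the primary mixed model uses baseline ISWT regardless of imbalance, either as a covariate or as an outcome with a common baseline mean across arms;
- any other prognostic covariates are named before the data are seen;
- the baseline-adjusted arm contrast at 6 weeks (post-PR) is the single primary estimate, and the unadjusted result is supportive.

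Either form of baseline adjustment removes the fault. The choice between them can take account of the allowance in the Sample size section, "Conservatively assuming up to 30% loss to follow-up at 6 weeks": the common-mean form keeps participants with only a baseline walk in the model, whereas the covariate form relies on the planned imputation for them.

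The cost is a sentence or two of text, matched in the SAP if one exists. Baseline ISWT is already scheduled for every participant, so no new data or visits are needed.

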### Adverse events

All adverse events and serious adverse events will be recorded on an adverse event log. This will be recorded within the study trial management paperwork, CRF and study database. The IDMC will review high-level safety data, which will be monitored at least every month and on an ad hoc basis as required. The NIHR RECHARGE Scientific Committee will be informed of all adverse events and determine the need to terminate the trial prematurely. Participants who experience any such event will receive the appropriate care.

### Patient and public involvement

We know from conversations with adults living with PTBLD that support after completing TB treatment is lacking and that these individuals continue to live with a reduced quality of life, including respiratory symptoms and social isolation. It is clear that these individuals would benefit from support to better manage their condition, which is what this project seeks to deliver. The PR intervention and trial are to be informed directly from people living with PTBLD and healthcare workers in Kyrgyzstan. The results of this work will be presented to patients and the public at dedicated dissemination events, including those hosted at the NCCIM, Bishkek and surrounding TB Hospitals.

### Ethics and dissemination

#### Research ethics approval

The study was approved 22 July 2019 by Ethics Committee of the NCCIM (reference number 17) [name], Bishkek, Kyrgyzstan. Ethics approval was also provided by the University of Leicester ethics committee on the 16 September 2019 ((reference number 22293, [contact]). Information about the study participants will be strictly confidential, and the names will be used only for internal reporting. No identifiable data will be published in any article.

#### Dissemination policy

Study results will be disseminated through appropriate peer-reviewed journals, national and international conferences and through social media. All participants will be provided a summary of the trial results. In February 2021, a National Scientific Medical Forum is planned and a National Respiratory Congress is planned in October 2021, which will also present the results of the study and disseminate information about the project. In addition, mobile rehabilitation schools are planned during 2021.
